### Setting

We are carrying out interventions in nursing homes in 8 European countries: Denmark, Greece, Hungary, Lithuania, Poland, Slovakia, Slovenia, and Spain. In each country, at least 10 nursing homes participate and a team of 4 HCPs in each nursing home are actively involved. Different types of professionals are involved in the health care of residents in the nursing homes: registered nurses, doctors that can be external or working in the facility part-time, health care assistants, or health care helpers. The participating nursing homes select the HCPs of their setting who actively take part in the study. These HCPs will, in turn, become trainers in their own nursing home after the intervention meetings.

### Project Methodology

A point prevalence audit is scheduled to assess the outcomes of the multifaceted intervention [27]. The audit is conducted in 2 separate 3-month periods: one before the intervention and another after. The initial registration occurred from February 2024 to April 2024, prior to the intervention, while the second registration will take place from February 2025 to April 2025, after the intervention (Figure 1). Throughout the audit, HCPs record anonymized information on UTIs antibiotic prescriptions on a chart. Sometime during the audit registration, participants are asked to also register the IPC measures in place in the nursing homes. Between the first and second audits, participants will attend a multifaceted intervention aimed at improving the prevention and management of infections in nursing homes (November 2024). The intervention and the data collection sheets are specifically designed for the study, based on preliminary work conducted in 2023.

**Figure 1 figure1:**
[figure not shown]
Audit Project Odense cycle in the IMAGINE (improving antibiotic use in nursing homes by infection prevention and control and antibiotic stewardship) project. IPC: infection prevention and control; PAR: participatory action research.

### Preliminary Study: Context Analysis

A preliminary study was conducted to identify potential areas for improvement in nursing homes across the 8 participating countries. The study involved a context analysis, which included interviews with HCPs working in nursing homes. These interviews focused on IPC practices, as well as antibiotic management. The aim is to explore the factors that contribute to the spread of infections within the target organizations.

Qualitative analysis was used to incorporate the perspectives of various nursing home HCPs in the development of educational materials. These materials facilitate communication between HCPs, residents, and their relatives when discussing the necessity and appropriate use of antibiotics for common infections. The analysis also helps identify any gaps in information that need to be addressed during the multifaceted intervention. Local coordinators within the 8 target countries of the IMAGINE project have contacted nursing home HCPs, who serve as the panel of experts for prioritizing areas of improvement. Their expertise guides the project’s focus on enhancing practices in nursing homes.

### Data Collection

A specific registration chart has been developed considering the characteristics and the quality improvement areas identified during the preparatory study performed in 2023. During the audit period, the participants are using the Audit Project Odense registration chart developed to record all the antibiotic prescriptions made in the nursing home. At most, 10 main groups and a maximum of 45 variables are used to describe the topic being investigated [27]. The main groups are lined up in a logical way, for example, focus of infection, symptoms, indwelling urinary catheter, diagnostic tests, treatment, and referral or not. The variables are exhaustive (include all possibilities) and exclusive (no overlapping), and all are in the same logic plan. One line is filled in for each case. As a rule, only ticks are allowed (no writing). At least 1 tick per main group is needed. Figure 2 depicts the definitive template used by IMAGINE. A short instruction sheet (maximum 1 page) has been provided for all participants. The instruction sheet specifies the registration period, the inclusion and exclusion criteria for the cases and briefly explains the content of each main group. Information about where to return the completed charts was given. A local contact person from the national teams is available for questions from the participants [27]. A pilot test of the chart was performed between October 2023 and November 2023 with 3 to 5 nursing home HCPs per country to ensure that the content of the registration chart was easily understood and to confirm that enough cases are available.

**Figure 2 figure2:**
[figure not shown]
Template used in the IMAGINE (improving antibiotic use in nursing homes by infection prevention and control and antibiotic stewardship) project for patients receiving antibiotics. Subject to subsequent changes that may arise during the pilot study.

### Multifaceted Intervention

Interventions that are expected to have the highest likelihood of success appear to align with the constructs of the normalization process theory, which explain the mechanisms of implementation [28]. These constructs include coherence (making sense of interventions), cognitive participation (engagement with the intervention), collective actions (enabling the intervention to take place), and reflexive monitoring (evaluating the costs and benefits). In the IMAGINE project, the multifaceted intervention aims to address all dimensions of the normalization process theory. It will achieve this by facilitating open discussions regarding variations in practice behaviors and by strengthening communication between HCPs, residents, and their families. Through these efforts, the intervention seeks to enhance the understanding and acceptance of the intervention among all stakeholders involved.

The multifaceted intervention will be composed by face-to-face and web-based activities, the latter in an asynchronous manner, enabling nursing home HCPs to engage in these activities at their own convenience. The main part of the training will be a 2-day intervention program consisting of (1) presentation of the first audit results and discussion with the rest of their colleagues in their respective countries, allowing self-reflection of their performance and discussing quality indicators associated with their practice; (2) AMR and IPC elements, with the participation of national experts; (3) discussion on AMS on how to improve the diagnosis of UTIs and the role of antibiotics for these infections; and (4) discussion of best practice case studies and practical issues.

The courses will be based on active discussion among participants, with the use of videos, leaflets, digital material, and role-playing, allowing fruitful discussion. This intervention will be recorded and adapted to a web-based environment. All material created for the intervention will be used to achieve three main objectives: (1) reinforcing the training of the HCPs, allowing them to revisit concepts whenever they need them; (2) training of the rest of the nursing home staff on IPC measures and AMS; and (3) after the end of the project, training of HCPs in other nursing homes in the country.

The intervention will be tailored to the nursing home setting. Achieving a significant behavioral change among multiple HCPs is essential for improving antibiotic prescribing in this population. To accomplish this, we will use the participatory action research methodology, which actively involves HCPs in the implementation of IPC and AMS interventions that are customized to their specific health care settings. This approach takes into account the local barriers and facilitators that may affect the successful implementation of these interventions [29]. The primary objective of the participatory action research is to generate practical knowledge that can be readily applied in local practice. By using this methodology, we aim to gain a better understanding of the complex decision-making process related to IPC practices and suspected health care–associated infections among frail elderly residents in nursing homes. It is important to consider the diverse elderly care settings across the various target countries, and participatory action research will help us navigate this heterogeneity [30].

National HCPs and stakeholders will participate to identify factors in the nursing home setting that contribute to increased risk of spread of infection and to determine national characteristics of nursing home management, diagnosis, and antibiotic prescription practices for nursing home residents and elderly patients with symptoms of infection. They will also work together to identify quality improvement areas related to hygiene, infection prevention, and inappropriate use of antibiotics; define priorities to be included when developing the educational material that will be used for facilitating communication between HCPs, residents, and relatives; and define an algorithm to be used for analyzing antibiotic inappropriateness in the different types of health care–associated infections.

### Data Analysis Plan

The data collected in the specific registration charts have a primary function at the individual level of health professionals, that is, helping them to improve their practice by reconsidering their treatment choices considering clinical evidence, guidelines, and professional consensus [31]. The second function is to analyze the data to evaluate the effect of the intervention. In each audit, data are recorded for all antibiotics prescribed during the 3-month period. We aim to record a minimum of 50 cases in each of the nursing homes recruited (at least 100 nursing homes), yielding an approximate number of 5000 cases in each registration period.

We will apply the chi-square test to determine the frequencies and appropriateness of prescriptions before and after the intervention and Student *t* test for the number of hygiene elements implemented in the nursing homes to test the null hypothesis of no effect of the interventions. To measure the potential reduction in UTIs, we will assume that antibiotics are always prescribed for these infections and every antibiotic is associated with a new episode of UTI [32]. The number of hygiene elements implemented will be compared with a threshold that will be defined during the participatory action research analysis. The appropriateness of antibiotic prescriptions will be defined according to an algorithm based on symptoms and patient characteristics that will be developed at the start of the project. We will also estimate the effect of the interventions on inappropriate prescriptions for UTIs using multilevel logistic regression models with 2 levels: cases and HCP participants, to allow for the fact that patients belonging to the same HCP are not independent of each other [33]. Statistical significance will be considered with *P*<.05. The data will be analyzed using the current version of the Stata statistical program (version 18, StataCorp LLC).

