**Methods:**

A before-and-after intervention study carried out in a minimum of 10 nursing homes in each of the 8 European participating countries (Denmark, Greece, Hungary, Lithuania, Poland, Slovakia, Slovenia, and Spain). A team of 4 professionals consisting of nurses, doctors, health care assistants, or health care helpers are actively involved in each nursing home. Over the initial 3-month period, professionals in each nursing home are registering information on UTIs as well as infection and prevention control measures by means of the Audit Project Odense method. The audit will be repeated after implementing a multifaceted intervention. The intervention will consist of feedback and discussion of the results from the first registration, training on the implementation of infection and prevention control techniques provided by experts, appropriateness of the diagnostic approach and antibiotic prescribing for UTIs, and provision of information materials on infection control and antimicrobial stewardship targeted to staff, residents, and relatives. We will compare the pre- and postintervention audit results using chi-square test for prescription appropriateness and Student *t* test for implemented hygiene elements.

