### Ethical Considerations

The study is conducted in accordance with the protocol, the Declaration of Helsinki, the principles of Good Clinical Practice, The General Data Protection Regulation (of the European Union) 2016/679 and the Human Research Act as well as other locally relevant regulations. Appropriate regulatory or ethical approval has been sought in each of the countries taking part in the study, and all study procedures started after gaining approval on the basis of the master protocol, translated where necessary to local language. In Spain, the coordinating country, the study protocol was approved by the Ethics Committee of Institut Universitari d’Investigació en Atenció Primària (IDIAP Jordi Gol), Institute of Research in Primary Health Care (23/080-P).

Nursing homes have been contacted by local coordinators that have explained the study and handed over the information, giving the nursing home time to read it and ask any questions. Informed consent was obtained from all participants. HCPs are participating voluntarily in this quality improvement project. No personnel data are collected from either HCPs or patients. A nursing home can withdraw from the project at any time without giving any explanation. The information gathered from the residents’ prescriptions are personally nonidentifiable data and we are collecting the minimum data set necessary for the study. Data are anonymized from the beginning, coded in the template with the code of the nursing home and a consecutive number for each antibiotic treatment. Individual patient consent is therefore not required.

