## Results

The local coordinators in each of the countries have already contacted all the nursing homes participating in the IMAGINE project, with a total of 109 nursing homes. All these nursing homes have already completed the first audit registration. The results of the first audit registrations will be available before the intervention takes place in November 2024. The overall results of the IMAGINE project will be available after summer 2025 and the results will be published by the end of 2025.

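### The before-after test of prescription appropriateness is an unadjusted chi-square on courses clustered in about 109 twice-audited nursing homes, so its nominal 5% error rate cannot be relied on

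*Protocol article*

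**What the plan says.** The Abstract (Methods) names one test for the prescribing result: "We will compare the pre- and postintervention audit results using chi-square test for prescription appropriateness". The Data Analysis Plan repeats it ("We will apply the chi-square test to determine the frequencies and appropriateness of prescriptions before and after the intervention") and states its purpose, together with that of the t test for hygiene elements: "to test the null hypothesis of no effect of the interventions". The threshold follows: "Statistical significance will be considered with" P<.05. No pairing, stratification or adjustment for nursing home or country is attached to the chi-square.

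The same section accepts that cases under one health care professional (HCP) are not independent. It adds a two-level logistic model (cases within HCPs) for inappropriate UTI prescriptions, introduced as something that will also be estimated. The model does not appear in the Abstract, and neither nursing home nor country is a stated level.

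On volume, the plan says: "We aim to record a minimum of 50 cases in each of the nursing homes recruited (at least 100 nursing homes". It puts the resulting total at about 5000 per audit. The Results section reports enrolment "with a total of 109 nursing homes", all of which completed the first audit. The Discussion says the same participants are compared before and after. Ethical Considerations describes records that carry a home code and a running treatment number, and mentions no HCP code.

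**The concern.** The pooled chi-square takes its variance from the number of courses alone. Courses from one home share prescribers, routines, case mix and national practice, so they carry less information than the same number of independent courses. Auditing the same homes twice cancels part of this shared component, but only the part that is unchanged between audits. Home rates that drift over the year for reasons unrelated to the intervention add variance that the chi-square does not see.

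The pooled share also weights each home by its case count. All antibiotic courses in each audit are recorded, so counts are not fixed. The share can therefore move because the case mix shifts between homes.

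At stake are the P value and interval for the main prescribing result. A second P value will exist for the same outcome from the multilevel model, and nothing says which one decides.

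**Working it through.** **The plan's own figure.** 100 homes × 50 cases = 5000 per period, which reproduces. With the 109 enrolled homes it is 109 × 50 = 5450. The article gives no ICC or power calculation to reproduce.

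**Inputs.** From the document: m = 50 cases per home and period; alpha 0.05 (two-sided assumed); the same homes in both audits. Assumed: within-period ICC ρ of 0.02, 0.05 or 0.10, and between-audit correlation of home rates r of 1, 0.8 or 0.5.

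**Formula.** With equal home sizes, the variance of the before-after difference relative to independence is

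DE = 1 + (m − 1)ρ − mρr,

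and the true type I error of the nominal 5% test is 2 × [1 − Φ(1.96/√DE)].

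Example, ρ = 0.10 and r = 0.8: DE = 1 + 4.9 − 4.0 = 1.9; 1.96/√1.9 = 1.42; type I error 15.5%.

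| ICC | r = 1 | r = 0.8 | r = 0.5 |
|---|---|---|---|
| 0.02 | DE 0.98, 4.8% | DE 1.18, 7.1% | DE 1.48, 10.7% |
| 0.05 | DE 0.95, 4.4% | DE 1.45, 10.4% | DE 2.20, 18.6% |
| 0.10 | DE 0.90, 3.9% | DE 1.90, 15.5% | DE 3.40, 28.8% |

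Simulation with 109 equal-sized homes, an assumed 60% inappropriate and no effect (4000 runs) agrees: at ICC 0.05, 9.8% (r = 0.8) and 18.5% (r = 0.5); at ICC 0.10, 15.4% and 28.2%.

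If only 25 of the cases per home were UTIs (assumed), ICC 0.10 gives DE 1.40 and 9.8% at r = 0.8, and DE 2.15 and 18.1% at r = 0.5. The problem is smaller but remains.

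**Volume shifts alone.** Set r = 1, so no home changes its rate, and let home volumes vary independently between audits. With a coefficient of variation of 0.3 or 0.6, the simulated type I error is about 8% or 15% at ICC 0.05, and about 10% or 21% at ICC 0.10.

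As an illustration, suppose half the cases come from homes at 40% inappropriate and half from homes at 80%. The pooled share is 0.5 × 40% + 0.5 × 80% = 60%. If the split moves to 55/45, it becomes 0.55 × 40% + 0.45 × 80% = 58%. With 5000 cases per period, z = 0.02/√(0.59 × 0.41 × 2/5000) = 2.03, P = .042, although no home changed its rate.

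**If the target is met.** Take an assumed fall from 60% to 36% (40% relative), 2500 cases per period and DE 3.4. Unadjusted z = 0.24/√(0.48 × 0.52 × 2/2500) = 17.0; divided by √3.4 it is 9.2. Significance survives.

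**Which adjustment works.** At ICC 0.10 and r = 0.5, a test stratified by home but blind to drift still rejected about 30% of the time, against 28% for the pooled chi-square. A paired home-level test held about 5%, and home-level cluster-robust variance held 5-6%.

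**The case against.** The strongest reply is that the plan does address clustering. The multilevel model is there because cases within an HCP are not independent, and it covers inappropriate UTI prescribing, which Aims makes the primary prescribing objective. The body text never formally ranks the chi-square above it. This stands: a reader might infer that the plan ignores clustering, and it does not. But the chi-square is the only prescribing test in the Abstract, and the Data Analysis Plan puts the test of no effect on it. The model clusters on a unit for which Ethical Considerations describes no code. The chart itself is a figure not shown, so an HCP code may exist; even then, home is not a stated level.

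A reader might also infer that the chi-square P value is always too small. It is not: with stable home rates and volumes the test is slightly conservative.

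A third tempting reading is that high-prescribing homes will drop out and create a spurious effect. The document says only "A nursing home can withdraw from the project at any time", an ordinary consent right. All 109 homes completed the first audit, and the stated intention is to compare the same participants, so differential withdrawal is possible but not shown. Nor is every volume shift an artefact: fewer courses in a high-prescribing home is itself movement on an objective framed as incidence of inappropriate use, and weighting by course is a legitimate choice of target. What remains is that the share and its P value can move without any home changing its rate.

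Finally, the practical consequence is limited if the effect is as large as targeted, and the study already declares its lack of a control group. That bears on severity. The limitations do not mention clustering.

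**Conclusion.** The point holds. The stated before-after test of prescription appropriateness ignores nursing home and the repeated audit, and its nominal 5% level cannot be relied on. With 50 cases per home and period and a between-audit correlation of 0.8 to 0.5, the true type I error is about 7-11% at ICC 0.02, 10-19% at 0.05 and 16-29% at 0.10. ICC and correlation are assumptions, because the document gives neither. With stable rates and volumes the error is about 4-5%; volume shifts push it up.

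The multilevel model mitigates this for the primary UTI outcome but is neither named as decisive nor clustered on home. The risk is a false-positive claim for a small change and intervals that are too narrow, not loss of the 40% target effect. It should be corrected, but it does not undermine the study as a whole.

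**What to change.** Name one primary analysis for prescription appropriateness: a logistic model with period and country as fixed effects and nursing home as the cluster. Its variance must let home rates drift between audits, through home-level cluster-robust standard errors or through random home plus home-by-period effects. Home as a stratum or a single random intercept is not enough, because neither captures the drift.

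Run the model in homes with both audits, or repeat it there as a check. Keep the pooled frequencies and chi-square as description only, and align the Abstract and the Data Analysis Plan.

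The cost is wording. The home code is already on each record, so no new data are needed. The downside is wider intervals.

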### Aims

The primary objectives of this study (IMAGINE project) are aimed at increasing the IPC elements implemented by 50% and decreasing the incidence of inappropriate antibiotic consumption for UTIs by 40%, with a subsequent 20% reduction in the incidence of UTIs. Different secondary objectives are planned: (1) reduction in inappropriate use of urinary catheters in nursing home residents; (2) reduction in the percentage of inappropriate antibiotic use for the prophylaxis of UTIs; (3) reduction in the number of Watch and Reserve antibiotics from the World Health Organization Access, Watch, Reserve classification; (4) improvement in the satisfaction of nursing home HCPs, residents, and relatives; (5) reduction in the incidence of health care–associated infections treated with antibiotics others than UTI; and (6) reduction in the percentage of hospital admissions.

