### Data Management

The collection of the audit data is performed on paper. The registration templates will be stored securely in in each participating nursing home and will be accessible only by study staff and authorized personnel. Charts will be transferred electronically to the Audit Project Odense service provider to be entered in a database [31]. Data from residents will be anonymously collected from the beginning and no identifiable or personal information will be gathered. Nursing homes will be identified by a code. Qualitative interviews will be audio recorded, transcribed, and translated, and any identifiable information will be deleted in the process. Translations will be transferred securely to the organization in charge of analyzing the results. Anonymized data from the survey will be stored for a minimum of 5 years after publication of the results. Anonymized project data will be shared for common analyses and presentation to the scientific community through publications and conferences.

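### The plan counts each antibiotic as a new UTI episode, so a changed or repeated course counts one infection twice; the before-after change is biased only if that happens at a different rate in the two audits

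*Protocol article*

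**What the plan says.** The Aims section of the protocol article lists among the primary objectives "decreasing the incidence of inappropriate antibiotic consumption for UTIs by 40%, with a subsequent 20% reduction in the incidence of UTIs". The Data Analysis Plan gives the only rule for counting UTIs: "we will assume that antibiotics are always prescribed for these infections and every antibiotic is associated with a new episode of UTI". A reference is cited for that assumption.

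The unit of recording is described in three ways:

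- Data Analysis Plan: "In each audit, data are recorded for all antibiotics prescribed during the 3-month period". The same paragraph then speaks of about 5000 cases per registration period.
- Data Collection: "One line is filled in for each case". The article does not say whether a case is an infection episode or a prescription.
- Ethical Considerations: entries are "coded in the template with the code of the nursing home and a consecutive number for each antibiotic treatment".

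On linkage, Data Management says "Data from residents will be anonymously collected from the beginning and no identifiable or personal information will be gathered". No resident code or episode code is described, and neither is a rule for merging entries that belong to one infection. The limitations in the Discussion cover diagnostic misclassification and the lack of a control group, but not this counting assumption.

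**The concern.** The rule is right for a UTI treated with a single course. It gives two infections for one UTI when the first agent is replaced, or when the same unresolved UTI is treated again, and the second course is registered separately. Here the infection is real and its treatment may be entirely appropriate; it is simply counted more than once. Restricting the count to appropriate, non-prophylactic courses would not remove the problem.

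At stake is the reading of the 20% target. A count of courses is the number of episodes times the courses per episode. A change in it shows a change in infections only if the second factor stays constant. Part of the intervention is "discussion on AMS on how to improve the diagnosis of UTIs and the role of antibiotics for these infections", and a secondary objective is "reduction in the number of Watch and Reserve antibiotics from the World Health Organization Access, Watch, Reserve classification". Both concern how UTIs are diagnosed and which agents are used, so they could change how often treatment is altered or repeated. With one group measured before and after, nothing in the design would separate such a shift from a change in infections.

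**Working it through.** **Inputs from the article.** At least 50 cases in each of at least 100 homes; target of a 20% reduction in UTI incidence; no control group. The planned size reproduces: 50 × 100 = 5000 cases per period (50 × 109 = 5450 with the homes enrolled).

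**Assumed inputs.** The documents do not say how often a UTI receives more than one course. Let s0 and s1 be the extra registered courses per true UTI episode in the first and second audit. Values of 0% to 20% are used for illustration only.

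**Step 1: the absolute count.** If E episodes occur, the rule counts E(1+s). The share of counted episodes that are not new infections is s/(1+s): 0.05/1.05 = 4.8% at s = 5%, and 0.20/1.20 = 16.7% at s = 20%. For scale, assume 2500 UTI courses per audit. This takes half of 5000, borrowing the nearly 50% urinary share that the Introduction cites from another survey. Then 2500 - 2500/1.05 = 119 and 2500 - 2500/1.20 = 417 counted episodes would not be new infections.

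**Step 2: the before-after change.** Apparent ratio = true ratio × (1+s1)/(1+s0).

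| s0 | s1 | Factor | Apparent change, no true change | Apparent change, true -20% |
|---|---|---|---|---|
| 10% | 10% | 1.000 | 0.0% | -20.0% |
| 10% | 8% | 1.08/1.10 = 0.982 | -1.8% | -21.5% |
| 15% | 5% | 1.05/1.15 = 0.913 | -8.7% | -27.0% |
| 5% | 15% | 1.15/1.05 = 1.095 | +9.5% | -12.4% |

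To produce the whole 20% target with no true change, the factor must be 0.80, for example s0 = 25% and s1 = 0%.

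**Step 3: could such an artefact reach significance?** With 2500 courses in the first audit (assumed) and a factor of 0.913, the second audit has 2283. Treating the counts as independent, z = (2500 - 2283)/√(2500 + 2283) = 3.14, beyond 1.96. A shift of that size would probably give P<.05, but it requires the rate of extra courses to fall to a third.

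**Step 4: what a correction can do.** Corrected ratio = observed ratio × (1+s0)/(1+s1). Setting s0 equal to s1 makes the last factor 1 and returns the uncorrected result. Varying them separately is informative. Suppose the observed change is -20% and s1 is estimated at 10%. With s0 = 0% the corrected change is 0.80 × 1.00/1.10 - 1 = -27.3%; with s0 = 20% it is 0.80 × 1.20/1.10 - 1 = -12.7%.

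**The case against.** **The error may cancel.** The outcome is a before-after change, and a stable rate of extra courses drops out exactly. A reader might infer from the training content that the intervention itself alters this rate. The documents do not say so: they mention diagnosis, the role of antibiotics and the choice of agents, but not switching, step-down or re-treatment. This stands. A biased change is a possibility, of unknown direction and size.

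**Key material is not shown.** The registration chart and the instruction sheet with the inclusion and exclusion criteria for cases are not available. They might exclude continuations or put two concurrent agents on one line. An extension of the same drug counts twice only if it is entered anew. This also stands. One cannot assert that every second agent is double counted, or that the first-audit chart lacked a field for changed treatment. What remains is the counting rule as written, which would not use such a field.

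**The illustrations are chosen.** The rates have no basis in the documents, and the larger figures need a threefold change. A modest shift, 10% to 8%, moves the result by 1.8%. This is a fair limit on the size.

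**The appropriateness test.** A reader might infer that the duplicates also spoil the comparison of appropriateness. They do not: that test is of prescriptions, so a second prescription is a legitimate unit. Correlation between entries is a separate, clustering question.

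**A larger problem lies in the same sentence.** Under the rule, an avoided inappropriate prescription also counts as a prevented UTI. With the Introduction's cited 60% inappropriate and the 40% reduction target, 0.60 × 0.40 = 24% fewer courses with no infection prevented. That mechanism is distinct. It does not answer the present point, but the relabelling proposed below helps with both.

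**Conclusion.** The point holds in a limited form. The article states a rule, rather than leaving one to another document, that equates antibiotics with UTI episodes. The rule feeds a primary objective, and the records described offer no way to undo it. The absolute number of UTIs is inflated to the extent that UTIs receive more than one registered course. The before-after change is biased only if that extent differs between the audits. This is plausible, in either direction, but not documented.

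The size cannot be fixed from the documents. With assumed rates of 5% to 15% it runs from -8.7% to +9.5% with no true change; a small shift gives about 2%. This does not show that a 20% fall would be an artefact. It shows that a fall in the count cannot by itself be reported as a fall in UTI incidence.

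**What to change.** 1. Name the outcome *antibiotic courses for UTI*, and do not report a fall in it as a fall in UTI incidence.
2. Reconcile the unit between Data Collection, the Data Analysis Plan and Ethical Considerations (case against antibiotic treatment). Define a UTI episode as the first course registered for that infection.
3. If the chart does not already capture it, add one tick to the second-audit chart for change or continuation of treatment of an episode already registered, with one line on the instruction sheet. This estimates s1. Keep the unadjusted count of courses as the like-for-like comparison between audits.
4. The first audit is complete. If its chart holds no such field, report any statement about incidence over a grid in which s0 varies independently of s1, for example 0% to 20% each. Do not set s0 equal to s1.

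The cost is one tick box, one instruction line and one sensitivity table. The second chart would differ from the first by one field, and the claim about incidence becomes a range. If the chart can no longer be changed, items 1, 2 and 4 can still be done, with both rates assumed.
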